### Outcome measurement

The primary outcomes is 6-minute walking test (6MWT). Secondary outcomes include pulmonary function tests (FEV1%, FEV1/FVC, MMEF, PEF), CAT score and mMRC score. Pulmonary function tests are performed by specialists. 6MWT is performed by trained research team members. Symptoms of breathlessness will be assessed using the mMRC and the CAT questionnaire will be used to assess quality of life. If the patient has an acute exacerbation, it will be recorded. Any changes in drug treatment of the patients will also be recorded. None of the outcome assessors will be aware of the patients’ grouping.

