### Follow-up

General information and observations will be collected from patients at the time they join the study. For the LG group, follow-up visits will be made once a week (telephone or WeChat) for the first 1 month and once every 2 weeks (telephone or WeChat) for the next 2 months after enrolment. By means of follow-up visit, patients will be reminded to exercise Liuzijue, and researchers can get to know the changes in their health condition and promptly help them to overcome the difficulties encountered in the process of exercising. Field follow-up visits is conducted 3 months and 6 months after admission to record changes in the patient’s outcome indicators for both CG and LG.

Patients will be followed up using a WeChat applet. The applet will help patients to clock in for training, do self-test health scales, upload and view test reports, initiate consultations with doctors, view health information and record acute exacerbations. Through the platform, doctors can view patients’ records such as punch cards, scale assessments and test reports, and contact patients for follow-up visits. At the end of each training session, patients will be asked to make a record on the applet. Furthermore, the number of follow-up visits is flexibly adjusted according to the patient’s punch card records.

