### Statistical analysis

Statistical analysis of the data will be performed using SPSS Statistics 26.0. Continuous variables with normal distribution will be described by mean and standard deviation. Continuous variables with non-normal distribution or ordinal variables will be described by median and interquartile range. Categorized variables will be summarized as counts and proportions. Continuous variables will be compared using Student’s t-test (normal distribution) or the Mann-Whitney U test / Wilcoxon rank test (abnormal distribution). Ordinal variables will be compared using Mann-Whitney U test/ Wilcoxon rank test. The categorical variables will be compared using Fisher’s exact test or the chi-squared test. Training-related effects will be assessed using a repeated ANOVA. All reported *P* values are two-sided, and *P* values < 0.05 is considered statistically significant.

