Liuzijue itself is a form of low-intensity aerobic exercise [25]. Aerobic exercise improves the function of respiratory and skeletal muscles, and enhances the patient’s exercise capacity [26]. Both low and high-intensity aerobic exercise can be clinically beneficial for COPD patients [27]. Besides, physical activity appeared to be an predictive indicator for COPD patients mortality [28]. Studies have shown that regular physical activity can reduce the hospitalization rate and mortality rate of COPD patients [29, 30]. As a form of exercise training, Liuzijue helps COPD patients establish a habit of exercise, which in turn improves patients’ outcomes.

The use of intention is also an integral part of Liuzijue training, which requires the trainer to relax the mind and body while imagining the essence of nature being inhaled while qi moves through the body and the turbid qi is exhaled. In the training of Liuzijue, the mind is focused on the breath, which is similar to the effects of mindful meditation [31]. Studies have shown that positive mindfulness training can influence the perceived internal awareness of key symptoms of COPD, such as breathlessness and coughing, resulting in better control of the patient’s symptoms [32] and relief of anxiety and depression in COPD patients [33].

This study has some innovative features. ACCP guidelines suggest that a longer pulmonary rehabilitation program (more than 12 weeks) will produce more sustained benefit than a shorter pulmonary rehabilitation program [27], so this study extends the intervention period to 3 months (12 weeks). Furthermore, this study extends observation period to 6 months (24weeeks) to observe whether patients benefited a long time after Liuzijue intervention. Maximal mid-expiratory flow (MMEF) is an indicator of the degree of small airway obstruction [34]. Previous studies have shown that COPD patients with a lower MMEF would exacerbated frequently [35]. This study attempts to observe whether Liuzijue training can improve the small airway function of patients. Previous studies have shown that labial contraction breathing has a more significant rehabilitation effect in COPD patients with low peak expiratory flow (PEF) [36]. What’s more, COPD patients have significantly improved their PEF after pulmonary rehabilitation with a thoracic exercise band [37]. This study observe whether Liuzijue training can improve patients’ PEF, or whether Liuzijue is more suitable for people with low PEF.

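### The primary outcome, 6MWT, has no stated primary visit, and the plan does not say which of its listed tests, or which ANOVA term, decides it

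*Protocol article*

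**What the plan says.** Outcome measurement defines the primary outcome in one line: "The primary outcomes is 6-minute walking test (6MWT". No visit is given, and nothing says whether the value or its change from baseline is meant.

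Follow-up sets two post-baseline assessments: "Field follow-up visits is conducted 3 months and 6 months after admission to record changes in the patient’s outcome indicators for both CG and LG". The Discuss section gives each a purpose. The intervention length is explained by a guideline ("so this study extends the intervention period to 3 months (12 weeks"), and the later visit is there because "this study extends observation period to 6 months (24weeeks) to observe whether patients benefited a long time after Liuzijue intervention". Neither visit is called primary.

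Statistical analysis first lists tests by type of variable: "Continuous variables will be compared using Student’s t-test (normal distribution) or the Mann-Whitney U test / Wilcoxon rank test (abnormal distribution". It then adds "Training-related effects will be assessed using a repeated ANOVA", without naming the outcome or the model term. One threshold covers every P value: P "values < 0.05 is considered statistically significant".

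Sample size uses a single comparison of two 6MWT means (418.71 against 483.62) with 80% power and two-sided alpha of 5%. The second mean is described as following training, but no visit is stated.

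**The concern.** A primary outcome needs a measure, a time point and one deciding comparison. Here only the measure is fixed. Two visits qualify and they answer different questions: the effect at the end of training, and what remains three months after it. Two kinds of analysis qualify as well. The repeated ANOVA offers group, time and group-by-time terms, and the time term alone does not compare the groups.

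Two things are at stake. If the 3-month and 6-month results disagree, a reader cannot tell from the text which is the trial's answer. And if the choice were made after seeing the data, the 5% level used to size the trial would not be the level at which the primary claim was tested. Groups formed by patient choice, as described under Study design, make a comparison fixed in advance more important.

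**Working it through.** **1. Reproduce the sample size.** Inputs from Sample size: means 418.71 and 483.62; spreads 66.19 and 67.30 (the second is labelled a standard error but is used here as an SD); 80% power; two-sided 5%; 20% dropout.

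- Difference: 483.62 − 418.71 = 64.91.
- Pooled SD: √[(66.19² + 67.30²)/2] = 66.75.
- Normal approximation: n = 2 × (1.960 + 0.842)² × 66.75² / 64.91² = 16.6, so 17 per group.
- Exact noncentral t: 17 per group gives 78.5% power and 18 gives 80.9%, so 18 evaluable per group.
- Dropout: 18 / 0.80 = 22.5, so 23 per group and 46 in total.

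This matches the article if 23 already includes dropout. If 23 were the number before dropout, it would give 89.7% power, and 23 / 0.80 = 28.75 would mean 29 per group, or 58 in total. The calculation covers one test at one time point.

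**2. Error rate if more than one result could count.** If the two visits were independent, 1 − 0.95² = 9.75%. Repeated 6MWT values are correlated, but the article gives no correlation, so 0.5 to 0.9 is assumed. The check simulated 40,000 trials per setting with no group effect, normal data at baseline, 3 and 6 months, and equal correlation between all visits. The table shows the percentage of trials with at least one P < 0.05 on 6MWT.

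| Correlation | n per group | t-test at 3 or 6 months | plus group-by-time term |
|---|---|---|---|
| 0.5 | 18 | 9.1 | 12.5 |
| 0.5 | 23 | 8.9 | 12.2 |
| 0.7 | 18 | 8.3 | 12.3 |
| 0.7 | 23 | 8.2 | 12.0 |
| 0.8 | 18 | 7.9 | 12.0 |
| 0.8 | 23 | 7.7 | 11.7 |
| 0.9 | 18 | 7.2 | 11.6 |
| 0.9 | 23 | 6.9 | 11.2 |

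A t-test at 3 months alone gave 4.7-5.0%, and the group-by-time term alone 4.9-5.1%. Either one, named in advance, holds the level. The excess comes only from leaving the choice open.

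**3. Cost of each way to close the gap.** With one visit and one test at 5%, 18 evaluable per group keep 80.9% power and 46 in total stands. If either visit were to be sufficient, a Bonferroni split to 0.025 each needs 22 evaluable per group (81.2% power). Then 22 / 0.80 = 27.5, so 28 per group and 56 in total. At 0.025, 18 evaluable per group give 71.5%.

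**The case against.** The strongest reply is that the article never sets up several chances of success. The t-test and rank-test sentence is a generic list by variable type and would also serve baseline comparisons. It does not say that a test is run at each visit. The ANOVA sentence can fairly be read as naming the efficacy analysis, which would remove both the choice of visit and the choice between tests. The P < 0.05 sentence is a reporting threshold and does not say that any significant 6MWT result makes the trial positive. This stands: a reader might infer that success may be claimed from either visit by either test, but the text does not state such a rule.

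The direction of the design is also fairly clear. Sample size refers to the mean after training, Intervention ends training at 3 months, and Discuss ties the 6-month visit to lasting benefit. That also stands, and it is why 3 months is the natural primary visit. But it remains implied, and Discuss presents the longer observation as one of the study's innovative features.

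An analysis plan that is not shown may settle the test and the ANOVA term. That answers part of the point. The visit, however, belongs to the definition of the primary outcome, which this article gives without it. Fig. 2 is not shown; the text says that it gives time points, not that it ranks them.

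Finally, the simulation assumes groups that differ only by chance. Here patients choose their group, so multiplicity is not the largest threat to the error rate. That is true, but it is a separate matter and does not fix the primary comparison.

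**Conclusion.** The point holds in a limited form. The primary visit for 6MWT is not stated, and the listed analyses are not tied to it, while the sample size assumes one comparison at 5%. The possible inflation is moderate: about 7-9% if a two-group test at either visit could count, and about 12% if the group-by-time term could count too. These figures depend on the assumed correlation of 0.5-0.9 and on reading the open choice as usable. They show what the wording permits, not the trial's actual error rate.

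Two stronger conclusions are not supported. The article does not say that any significant 6MWT result is a success, so the 5% level is not assured rather than shown to be broken. Nor do unadjusted P values on the secondary outcomes add to the problem: they are already labelled secondary and do not bear on the primary claim.

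**What to change.** In Outcome measurement, state that the primary outcome is 6MWT at 3 months (end of training), and that 6MWT at 6 months is a secondary outcome for persistence.

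In Statistical analysis, state that the primary comparison is the between-group difference in 3-month 6MWT, adjusted for baseline 6MWT, at two-sided 5%, and that the repeated ANOVA is supportive, with the term of interest named.

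The cost is about one sentence in each section. The 23 per group need not change if it is stated to include the 20% dropout; the 80.9% power refers to the unadjusted t-test on 18 evaluable per group. The real price is that a 6-month result alone can no longer make the trial positive. If the sponsor wants either visit to be sufficient, the level must be split and the total rises to about 56.

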### Statistical analysis

Statistical analysis of the data will be performed using SPSS Statistics 26.0. Continuous variables with normal distribution will be described by mean and standard deviation. Continuous variables with non-normal distribution or ordinal variables will be described by median and interquartile range. Categorized variables will be summarized as counts and proportions. Continuous variables will be compared using Student’s t-test (normal distribution) or the Mann-Whitney U test / Wilcoxon rank test (abnormal distribution). Ordinal variables will be compared using Mann-Whitney U test/ Wilcoxon rank test. The categorical variables will be compared using Fisher’s exact test or the chi-squared test. Training-related effects will be assessed using a repeated ANOVA. All reported *P* values are two-sided, and *P* values < 0.05 is considered statistically significant.

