**Discussion:**

This study quantified the effect of Liuzijue on the pulmonary rehabilitation of COPD patients in the stable phase of the disease, and provided a basis for the use of Liuzijue in COPD patients.

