## Methods/design

### Study design

This study is a multicenter, non-randomized, prospective study. There are 3 centers in this study, including the First Affiliated Hospital of Zhejiang Chinese Medicine University, the Affiliated Hospital of Jiangxi University of Traditional Chinese Medicine and the Affiliated Hospital of Chengdu University of Traditional Chinese Medicine. Patients will be divided into a control group (CG) and a Liuzijue group (LG) based on their willingness to learn Liuzijue. None of the outcome assessors will know the grouping of the patients. Participants in this study will be collected from stable COPD patients who are outpatients or inpatients since September 2021. The protocol has been registered in the China Clinical Trial Registry (registration number: ChiCTR2100048945) and approved by the Ethics Committee of Zhejiang Provincial Hospital of Chinese Medicine (Ethics number: 2019-KL-095-06). Informed consent will be obtained from all participants before they participate in the study. The research process is shown in Fig. 1, and the time point of the research is shown in Fig. 2. The protocol follows the SPIRIT 2013 checklist, provided in Additional file 1: SPIRIT 2013 checklist.

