There are some limitations to this study. First, as the intervention factor is Liuzijue training, it is difficult to blind the participants, leading to biased results. Second, the compliance of patients with Liuzijue training at home will be lower than the outpatient or ward-based intervention. To deal with this, researchers will monitor patients’ WeChat applet training records, timely follow up patients with low compliance, and encourage them to overcome difficulties and complete daily training. Thirdly, Liuzijue is a traditional Chinese qigong, which may hinder its application and spreading in other countries.

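### Patients choose their own group, yet the stated tests adjust for nothing; on follow-up values, or on a repeated-ANOVA group main effect, a baseline head start counts as a Liuzijue effect.

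*Protocol article*

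**What the plan says.** The protocol article, under Study design, calls the study non-randomized and gives the allocation rule: "Patients will be divided into a control group (CG) and a Liuzijue group (LG) based on their willingness to learn Liuzijue". There are three centres, and both inpatients and outpatients are eligible.

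Under Outcome measurement, "The primary outcomes is 6-minute walking test (6MWT") is named. Under Follow-up, "General information and observations will be collected from patients at the time they join the study", and then "Field follow-up visits is conducted 3 months and 6 months after admission to record changes in the patient’s outcome indicators for both CG and LG".

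Under Statistical analysis, "Continuous variables will be compared using Student’s t-test (normal distribution) or the Mann-Whitney U test / Wilcoxon rank test (abnormal distribution"). Ordinal variables get rank tests and categorical variables get Fisher's exact or chi-squared tests. Training-related effects get a repeated ANOVA. No section mentions a covariate, matching, weighting, stratification or a centre term.

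The limitations, near the end of the discussion, begin "First, as the intervention factor is Liuzijue training, it is difficult to blind the participants, leading to biased results" and go on to home compliance and uptake in other countries. Confounding by self-selection does not appear. The abstract's discussion says "This study quantified the effect of Liuzijue on the pulmonary rehabilitation of COPD patients in the stable phase of the disease".

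**The concern.** A two-sample test estimates a treatment effect only if the groups would have had the same outcome without the treatment. Allocation by willingness gives no such assurance. The selection also acts close to the endpoint: the intervention is daily exercise, the primary outcome is walking distance, and people willing to take up exercise may well walk further, or be more motivated, from the start.

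At stake is the primary comparison. An unadjusted difference in follow-up 6MWT mixes any head start with any Liuzijue effect and can be significant when the exercise does nothing. The observations taken at entry have no stated role in the comparison, although they could reduce the problem.

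**Working it through.** **Inputs from the Sample size section.** Means 418.71 and 483.62 m, spreads 66.19 and 67.30 m, 80% power, two-sided 5% alpha, 20% dropout, 23 per group, 46 in total. The 67.30 is labelled a standard error but is treated here as an SD, which is the reading that reproduces the plan's figure.

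**The plan's own figure.**
- Difference = 483.62 − 418.71 = 64.91 m.
- Pooled SD = √[(66.19² + 67.30²)/2] = 66.75 m, so d = 64.91/66.75 = 0.97.
- Noncentral-t power is 78.5% at 17 per group and 80.9% at 18.
- 18/0.8 = 22.5, rounded up to 23 per group, 46 in total.

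The stated size reproduces and is not in dispute. It does treat the whole 64.91 m as a Liuzijue effect.

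**Assumptions.** The article gives neither a baseline gap nor a correlation between visits. I take 18 evaluable per group, SD 66.75 m at every visit, equal correlation r = 0.7 or 0.8 between visits, zero Liuzijue effect, and a baseline gap b of 0.3 SD (20.0 m) or 0.5 SD (33.4 m). Two cases are shown. In one, the gap partly regresses and follow-up carries r × b, so baseline 6MWT carries all the imbalance. In the other, the gap persists in full.

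**t-test on follow-up 6MWT.** Standard error = 66.75 × √(2/18) = 22.25 m. The noncentrality is the follow-up gap divided by 22.25, with 34 df.

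| Baseline gap | Case | Bias (m) | Error |
|---|---|---|---|
| 20.0 m | partly regresses, r = 0.7 / 0.8 | 14.0 / 16.0 | 9.4% / 10.8% |
| 20.0 m | persists in full | 20.0 | 14.1% |
| 33.4 m | partly regresses, r = 0.7 / 0.8 | 23.4 / 26.7 | 17.5% / 21.5% |
| 33.4 m | persists in full | 33.4 | 30.8% |

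**Repeated ANOVA, group main effect over baseline, 3 and 6 months.** The SD of a patient's three-visit mean is 66.75 × √[(1 + 2r)/3] = 59.7 m (r = 0.7) or 62.1 m (r = 0.8). The mean gap is b(1 + 2r)/3 if it partly regresses and b if it persists.
- 20.0 m gap: error 12.3% / 12.9% (partly regresses) and 16.5% / 15.6% (persists).
- 33.4 m gap: error 25.6% / 27.4% and 37.1% / 34.7%.

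Simulations of the same settings agree to within about one percentage point.

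**Change from baseline (group-by-time with two visits).** If the gap persists, it cancels and the error is 5%. If it partly regresses, the bias is −(1 − r)b, that is −4.0 to −10.0 m, against Liuzijue. The SD of change is 66.75 × √(2 − 2r), and the two-sided error is 5.9–8.7%.

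**ANCOVA on baseline 6MWT.** If the gap partly regresses as above, there is no bias and the error stays near 5%. If it persists in full, a bias of (1 − r)b = 4.0 to 10.0 m in favour of Liuzijue remains, with simulated error of 6–9%.

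**Precision with no imbalance, baseline 6MWT as the only covariate.** The 95% half-width of the t-test is 2.03 × 22.25 = 45.2 m. Multiplying the standard error by √(1 − r²) gives about 36, 32 and 27 m at r = 0.6, 0.7 and 0.8.

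**The case against.** The strongest reply concerns the repeated ANOVA. It is assigned to training-related effects, and the follow-up visits are said to record changes, so the natural reading is a group-by-time test, in which a constant head start cancels. A reader might infer that the repeated ANOVA as planned also turns a head start into a Liuzijue effect. The article does not support that: it does not name the term tested, the charge holds only for the group main effect, and where the gap partly regresses the change contrast is biased against Liuzijue. What remains is that the safer term is not secured, and that even this term does not adjust for severity, age or centre.

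Second, the sentence on t-tests and rank tests is a general list by variable type. It does not say whether baseline values, follow-up values or changes are compared, so the t-test figures are conditional on follow-up values.

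Third, ANCOVA is not a complete remedy. It is unbiased here only when baseline 6MWT carries the imbalance, and no model removes unmeasured motivation. This stands and shapes the fix.

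Fourth, the design is openly called non-randomized, and an analysis plan not shown might add adjustment. Disclosing the design does not adjust the analysis, though, and the article is not silent on method: it fixes named tests that suit exchangeable groups.

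**Conclusion.** The concern holds in a limited form. The study compares self-selected groups, fixes only unadjusted tests, leaves the repeated-ANOVA term open and omits self-selection from its limitations. For a t-test on follow-up 6MWT, an assumed 20–33 m head start raises the false-positive rate from 5% to about 9–22% if the gap partly regresses and 14–31% if it persists. For a group main effect the rates are about 12–27% and 16–37%. These figures rest on 18 evaluable patients per group, SD 66.75 m and correlations of 0.7–0.8. The gap and the correlation are assumptions.

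Two stronger conclusions may be tempting. One is that the groups will differ at baseline and the result will be biased; the article contains no baseline data, so it shows only that the stated tests give no protection if they do differ. The other is that baseline adjustment restores a causal comparison, which it cannot do while motivation is unmeasured.

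**What to change.** Before results are seen:

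- Make the primary analysis a baseline-adjusted comparison of 6MWT (ANCOVA or mixed model) with baseline 6MWT and centre, plus at most one or two prognostic covariates such as age and baseline FEV1%. With about 36 to 46 patients, a longer list is hard to support. Report the adjusted mean difference with its 95% CI.
- Add the group-by-time (change) contrast as a sensitivity analysis, because it is free of bias when a gap persists in full, where ANCOVA is not.
- Adjust the continuous secondary outcomes and CAT for their own baseline values. Keep the unadjusted tests as descriptive.
- Report standardised baseline differences between the groups.
- List self-selection and residual confounding, including unmeasured motivation, as a limitation, and word the conclusion as an adjusted association.

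The cost is a few degrees of freedom and a more cautious conclusion. Baseline values and eligibility data should already be in hand, so no extra patients or visits are needed. The narrowing from 45 m to 27–36 m applies to adjustment for baseline 6MWT alone with no imbalance; it was not computed for the fuller model.

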### Sample size

The sample size is calculated based on the primary outcome (6MWT) using PASS15.0 software. According to the previous literature [17], the mean for the control group is estimated to be 418.71 with a standard deviation of 66.19. After Liuzijue exercising, the mean for the experimental group is 483.62 with a standard error of 67.30. With a power of 80% and an alpha of 5% (two-sided), the minimum sample size per group is 23. Given a drop-out rate of 20%, the minimum sample size in total is 46.

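### Classical repeated ANOVA keeps only patients with all three visits; a mixed model on all observed visits, tested by change-from-baseline contrasts, would serve better

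*Protocol article*

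**What the plan says.** The Statistical analysis section of the protocol article gives one sentence on the effect of training: "Training-related effects will be assessed using a repeated ANOVA". It names neither the factors nor the term to be tested. For other comparisons it says "Continuous variables will be compared using Student’s t-test (normal distribution) or the Mann-Whitney U test / Wilcoxon rank test (abnormal distribution"), again without a baseline term. The software is fixed: "Statistical analysis of the data will be performed using SPSS Statistics 26.0".

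The Follow-up section has observations collected at entry and field visits at months 3 and 6 for both groups. The Outcome measurement section makes 6MWT the primary outcome and names no primary visit. The Sample size section says "With a power of 80% and an alpha of 5% (two-sided), the minimum sample size per group is 23", then continues "Given a drop-out rate of 20" percent and gives a total of 46. Under Study design, patients enter a group according to whether they are willing to learn Liuzijue.

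**The concern.** Classical repeated-measures ANOVA (SPSS GLM, for example) works on complete rows. A patient who walks at entry and month 3 but misses month 6 contributes nothing, and the observed month-3 value is lost.

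Such loss may not be random. The Discussion expects lower compliance at home, the Safety section has patients stop training on any discomfort, and only the Liuzijue group receives the regular reminder contacts. Retention could therefore differ between groups and could depend on response. If poor responders in the Liuzijue group leave, a completers' analysis favours Liuzijue.

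The tested term also matters. With entry as a time level, the group main effect averages a pre-training value with two later ones, and these groups were formed by choice. The group-by-time F test avoids that, but over three visits it is a 2-df omnibus test and gives no estimate at a named visit.

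**Working it through.** **Inputs from the Sample size section.** For controls, "the mean for the control group is estimated to be 418.71 with a standard deviation of 66.19". For the Liuzijue group, "the mean for the experimental group is 483.62 with a standard error of 67.30". The figure 67.30 is read as a standard deviation, because the stated sample size reproduces on that reading. Power is 80%, two-sided alpha 5%, drop-out 20%.

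**The plan's own figure.**
- Difference: 483.62 − 418.71 = 64.91 m.
- Pooled SD: √[(66.19² + 67.30²)/2] = 66.75 m.
- Two-sample t-test: 18 per group gives 80.9% power (17 gives 78.5%).
- Drop-out: 18/0.8 = 22.5, so 23 per group and 46 in total. This matches, so 23 already includes the drop-out allowance.

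**Patients used.** 0.20 × 46 = 9.2, so about 9 are excluded and 37 remain complete. A model on all observed visits has these month-3 values:

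| When the 9 are lost | Repeated ANOVA | Mixed model, month 3 | Mixed model, month 6 |
|---|---|---|---|
| All before month 3 | 37 | 37 | 37 |
| About half after month 3 | 37 | 41 | 37 |
| All after month 3 | 37 | 46 | 37 |

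**Bias if loss depends on response.** This is a simulation under no true effect, with 23 per group and SD 66.75. Five Liuzijue patients are lost after month 3 from the 10 with the poorest response, and five controls are lost at random. The pattern and the correlations are assumptions. Completers' difference in change at month 3:

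| Correlation | Bias | False positives |
|---|---|---|
| 0.5 | about +16.5 m | about 11% |
| 0.7 | about +12.3 m | about 11% |
| 0.9 | about +7.3 m | about 11% |

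Repeat runs vary by a few tenths of a metre and stay within 10–12% false positives. At 0.7 the bias is 12.3/64.91 = 19% of the planned effect. The group-by-time F test on completers also rejects in about 9%, so choosing the interaction does not cure the deletion.

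Comparisons at correlation 0.7:
- Change scores on all month-3 data: bias +0.1 m, 4.9% false positives.
- Random loss in both groups: completers' bias about 0, 5.0%.
- Same selective loss but before month 3: a baseline-adjusted analysis of the remaining data is still biased by +10.8 m, 9.6%.

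**Main effect, if entry is a time level.**
- Sustained effect: (0 + 64.91 + 64.91)/3 = 43.3 m. Effect gone by month 6: 64.91/3 = 21.6 m.
- SD of a patient's three-visit mean: 66.75 × √[(1 + 2ρ)/3]. With 18 per group and a sustained effect, power is 64%, 56% and 50% for ρ = 0.5, 0.7 and 0.9. The change contrast (mean of months 3 and 6 minus entry) has 91%, 99% and 100%.
- No effect and an assumed 20 m baseline gap: the main effect rejects in 19%, 17% and 15%; the change contrast in about 5%.

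**Baseline as covariate under self-selection.** If groups differ by D at entry and simply stay apart, the baseline-adjusted difference is biased by (1 − ρ) × D. At ρ = 0.7, D = 20 m gives 0.3 × 20 = 6 m and D = 40 m gives 0.3 × 40 = 12 m, with about 7% and 12–13% false positives. The change contrast stays near 0 m and 5%.

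**The case against.** The article is condensed and no analysis plan is shown. Factors, contrasts and missing-visit rules are commonly left to that plan, so their absence is not a finding. That stands. The point concerns the method the article does name and what its classical form does with incomplete rows.

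The planned t-tests or rank tests, if applied at months 3 and 6, would use every observed value and give a difference at a named visit. The article does not spell out that use and assigns training effects to the repeated ANOVA, but this does limit how much is lost.

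The bias figures need selective loss confined to the Liuzijue group and falling after month 3. Nothing in the protocol says non-compliers leave the study, and the Follow-up section and Discussion describe active pursuit of low compliers. This stands: the size is conditional.

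A reader might infer three stronger things that the documents do not support:
- That the plan's group effect is diluted to 43.3 m. This needs entry as a time level and the main effect as the test; the article states neither, and the interaction term is free of the dilution.
- That the analysis does favour Liuzijue. No drop-out pattern is given.
- That a mixed model with baseline as covariate cures everything at no cost. Under self-selection, baseline adjustment assumes equal expected follow-up at equal baseline, while the change contrast assumes parallel trends. The documents allow neither to be tested.

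**Conclusion.** The point holds in a limited form. The named method, in its classical form, would exclude about 9 of 46 patients under the plan's own drop-out figure and discard any month-3 walk from patients lost later. The certain cost is precision, to the extent that loss falls after month 3. A bias of about +7 to +17 m with 10–12% false positives arises only if later loss in the Liuzijue group depends on response, over assumed correlations of 0.9 to 0.5. The main-effect problem is conditional on an unstated choice and is avoided by testing the group-by-time contrasts. The sample size of 46 is unaffected. This is a worthwhile, inexpensive improvement and not a fatal flaw.

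**What to change.** Replace the repeated ANOVA with a linear mixed model (SPSS MIXED):
- Outcomes: 6MWT at entry, month 3 and month 6.
- Fixed effects: group, visit, group-by-visit and centre.
- Unstructured covariance over the three visits, with a stated small-sample degrees-of-freedom method, since only about 18 patients per group may be complete.
- All observed visits of all patients, in the group they entered.
- Report the between-group difference in change from baseline with 95% CI at month 3 and at month 6.
- Sensitivity analysis: the same comparison adjusted for baseline 6MWT.

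The cost is a change of wording and slightly more analysis work; software, data and sample size stay the same. The limits should be stated with the method: the model relies on missing at random, recovers no follow-up for patients lost before month 3, and does not remove confounding from patients choosing their group. The article's limitations should acknowledge that confounding.
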